## Abstract

**Background:**

Childhood obesity is a major public health problem, with one third of America’s children classified as either overweight or obese. Obesity prevention and health promotion programs using components such as wellness coaching and home-based interventions have shown promise, but there is a lack of published research evaluating the impact of a combined home-based and wellness coaching intervention for obesity prevention and health promotion in young girls. The main objective of this study is to test the feasibility of such an intervention on metrics related to recruitment, intervention delivery, and health-related outcome assessments. The secondary outcome is to evaluate the possibility of change in health-related psychosocial, behavioral, and biomedical outcomes in our sample of participants.

**Methods/design:**

Forty girls who are overweight or obese (aged 8–13 years) will be recruited from a Midwestern college town. Participants will be recruited through posted flyers, newspaper advertisements, email, and social media. The volunteer convenience sample of girls will be randomized to one of two home-based wellness coaching interventions: a general health education condition or a healthy eating physical activity skills condition. Trained female wellness coaches will conduct weekly hour-long home visits for 12 consecutive weeks. Assessments will occur at baseline, post-intervention (3 months after baseline), and follow-up (6 months after baseline) and will include height, weight, waist circumference, body composition, pulmonary function, blood pressure, systemic inflammation, physical activity (Actical accelerometer), and self-reported survey measures (relevant to fruit and vegetable consumption, physical activity, and quality of life).

**Discussion:**

This study will evaluate the feasibility of home-based wellness coaching interventions for overweight and obese girls and secondarily assess the preliminary impact on health-related psychosocial, behavioral, and biomedical outcomes. Results will provide information regarding the feasibility of this new model for use in girls as an approach to reduce the burden of overweight and obesity toward the prevention of chronic disease.

**Trial registration:**

NCT01845480

**Electronic supplementary material:**

The online version of this article (doi:10.1186/s40814-016-0066-y) contains supplementary material, which is available to authorized users.

## Background

Approximately one out of every three children in the USA is overweight or obese [1]. Obese children are more likely than healthy weight children to have detrimental health outcomes, including high blood pressure, dyslipidemia, type 2 diabetes, and psychosocial problems [2–4]. Additionally, overweight and obese children are at a significantly greater risk of adult obesity, compared to children at a healthy weight [5]. This tracking of obesity into adulthood may lead to the development of more severe health outcomes [6]. In addition to health problems related to obesity, there is considerable financial burden associated with childhood obesity; medical costs from youth into adulthood are estimated at approximately $19,000 more per obese child, in comparison with healthy weight children [7]. As such, early interventions that target obesity treatment and prevention are warranted.

Successful childhood obesity interventions aim to regulate body fat and weight, while allowing for further growth [8] in ways that promote the persistence of healthful behaviors throughout the developmental years [9]. The goal is typically not weight loss but rather to achieve increases in height while slowing weight gain. Secondary prevention measures may focus on reducing the impact of childhood obesity by slowing or reversing the weight gain through the building of healthful behaviors. Secondary prevention techniques may include self-efficacy and skill-building for behaviors related to nutrition and physical activity [10]. Given that obesity may result from prolonged positive energy imbalance, interventions typically promote increased energy expenditure or appropriately balanced caloric intake, which can each be considered independent avenues to improve obesity outcomes. It is critical that childhood obesity interventions are handled with “kid gloves,” in that great care is taken to not stigmatize the individuals, and to ensure that quality of life is considered alongside weight status and healthful behaviors.

Both boys and girls are impacted by problems associated with obesity and could benefit from interventions and programs targeting health promotion. Girls, in particular, may do well with targeted health promotion and obesity prevention programs for a number of reasons. First, they are less physically active than boys, and this comparison becomes more disparate with increasing age, not only in terms of overall amount of physical activity but also in vigorous intensity physical activity [11]. Second, overweight and obese adolescent girls are more likely than healthy weight girls to use dysfunctional methods to try to control their weight [12]. Given the dysfunctional weight control efforts and special concerns within this population, it makes sense to develop health promotion and obesity prevention interventions that are uniquely tailored to meet the needs of girls.

Obesity prevention efforts, both primary and secondary, have been studied in a variety of settings, including during and outside of the school day. Given that children are exposed to so many different settings over the course of their childhood, there are a host of factors that may play a role in the potential of a given environment to be obesogenic. Specifically, the home environment functions as a major influence in a child’s dietary and physical activity behaviors [13], with US children consuming approximately two thirds of their daily calories in the home [14] and the physical and social environment of the home playing a role in children’s physical activity and sedentary levels [15]. Evidence shows that obesity prevention interventions delivered within the home setting can be effective in reducing body mass index in youth, specifically when education sessions and information are provided regarding healthful behavior change in physical activity and nutrition [16]. It has been suggested that obesity prevention programs may not be effective or sustainable without impacting the home environment of a child [17]. Additionally, interventions conducted within the home offer certain advantages when compared to center-based intervention delivery. Potential barriers to program participation can be limited with a home-based intervention, including location, transportation, childcare, and work obligations [18]. Additionally, it has been shown that attendance for center-based obesity prevention and treatment interventions tends to drop off quickly, with many barriers to participation being cited [19]. As a result, there is a need for additional research examining the impact of childhood health promotion and obesity interventions that are delivered within the home setting, where participation barriers can be minimized.

One type of health promotion and obesity prevention strategy that has shown success is behavior change through wellness coaching, which is a relatively new and emerging research area. In the wellness coaching model, individuals work with coaches to determine personal goals in a client-centered setting, using steps that lead to sustainable behavior change [20]. Successful wellness coaching practices have utilized several theoretical models and techniques, including social cognitive theory, self-determination theory, and motivational interviewing [21]. Components of effective wellness coaching may include client-chosen goal setting, affirmation, and activities to develop self-efficacy and intrinsic motivation. The ways in which wellness coaching has been implemented are quite diverse, as there has been success across various age groups and delivery sources (by phone, in person, online). Wellness coaching has shown promise for improving health behaviors related to chronic disease prevention [22], childhood obesity [23], dietary intake, and physical activity [24], among other health-related outcomes. Nutrition education combined with behavior change counseling has been shown to reduce body mass index in overweight and obese adolescents [25]. Additionally, a health coaching intervention that focused on nutrition and was delivered to families resulted in improved dietary intake and weight control [24]. A recent review concluded that health coaching can be effective for weight control, physical activity levels, and improved physical health, among other positive outcomes [26]. Coaching strategies may range from teaching clients general health education to more comprehensive plans that integrate skill-building and mastery experiences. Because education alone is typically not sufficient for behavior change, the skills-based component offers opportunity for capacity building, self-efficacy, self-regulation, and environmental change [27]. Although self-regulation skills can be developed within various childhood settings, wellness coaching that helps build these skills within the home environment provides a unique opportunity to target distinct mediators of behavior change that are most relevant to the home. Specifically, when children are able to learn self-regulation and environmental change skills that they can apply within the home setting, they may be better equipped to influence, control, and improve their home environment and associated health-related behaviors.

Although there is evidence to suggest that wellness coaching and home-based interventions can be effective as separate strategies for health promotion and obesity prevention, there is a lack of research examining the combination of the two, specifically a one-on-one, home-based, wellness coaching intervention for young girls. Therefore, our objective is to evaluate a new model, which consists of a wellness coaching intervention delivered within the home environment for young females. For the purposes of this paper, the term home-based refers to interventions delivered within the home and should not be confused with interventions delivered in alternate settings that intend to impact the home as a behavior setting.

The primary objective of this one-on-one, home-based wellness coaching intervention is to evaluate the feasibility metrics related to recruitment, intervention delivery, and health-related outcome assessments. These primary outcome feasibility assessments will include:The number of participants we are able to recruit from the local area and surrounding townsThe length of time required to recruit 40 eligible participantsThe number and percentage of wellness coaching sessions delivered within the home settingFidelity of intervention deliveryParticipant and parent satisfaction with intervention deliveryAdverse effects associated with the interventionThe number of participants who complete post-intervention and follow-up laboratory assessments

As a secondary outcome, we also seek to evaluate the preliminary impact of the intervention on change in girls’ health-related psychosocial, behavioral, and biomedical outcomes. Two arms of the intervention will be implemented: a healthful eating and physical activity (HEPA) skills condition and an active comparison group representing a general health education (HE) condition. We hypothesize that both intervention arms will be successful in recruitment and retention of participating families and delivery of the intervention sessions by trained college-aged research assistants and that both of the coaching conditions will be well received and appreciated by participating families.

## Methods/design

### Study design

As shown in Fig. 1, this study is a two-arm, parallel randomized trial comparing two home-based coaching interventions on primary feasibility outcomes related to recruitment, intervention delivery and acceptance, and health outcome assessments, with secondary, preliminary measures related to health-related psychosocial, behavioral, and biomedical outcomes of female children. The home-based, wellness coaching intervention period will last for 12 weeks, with laboratory assessments at baseline, post-intervention (3 months after baseline), and at follow-up (6 months after baseline). A 6-month follow-up period was chosen to evaluate the feasibility of having participants return to the laboratory for an assessment following the conclusion of the intervention. A fully powered study examining the impact on health outcomes may employ a longer-term follow-up to assess maintenance of behavior change and subsequent changes in health outcomes.

**Fig. 1 Fig1:**
[figure not shown]
Study flow diagram for The Wildcat Wellness Coaching Trial

### Study population

Participants for this study are 40 females aged 8 to 13 years. All girls will have a body mass index (BMI) at or above the 85th percentile (overweight or obese) of gender-specific, age-adjusted growth charts and must reside within 20 miles of Manhattan, KS (Kansas State University). Exclusion criteria require that the girls do not have developmental delays, psychiatric problems, or any illness, injury, or condition that prevents them from participating in moderate-to-vigorous physical activity. Finally, the participants cannot be taking weight-altering medication or be participating in any other weight control program. There will be no inclusion/exclusion criteria related to socioeconomic status or ethnicity. Parental consent and child assent will be obtained from all participants prior to their participation in the study. Kansas State University Institutional Board of Human Ethics approval has been obtained, and all study methods will comply with the Declaration of Helsinki.

### Recruitment

Parents of girls interested in a health promotion program will be recruited in various ways, including posted flyers, newspaper advertisements, social media, and word of mouth. Parents who are interested in having a daughter participate in the program will contact the principal investigator to obtain further information regarding the program and associated research study and an anticipated timeline for when their assessments and home visits will begin.

### Randomization

Rolling recruitment will be implemented, and participants meeting the inclusion criteria will be block-randomized using an online randomization program into one of two wellness coaching conditions, in blocks of four, with a 1:1 allocation ratio. The principal investigator will oversee the randomization process and will keep allocation concealed until baseline assessments have been completed. Research assistants collecting assessment data will be blinded to group randomization over the course of the study. Blinding of the study participants to their group assignment will not be possible due to the nature of the intervention itself, but participants will not know their assigned condition until after baseline assessments.

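### Fixed blocks of four, overseen by the person families first contact, let anyone who knows the earlier assignments in a block deduce about a third of the rest

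*Protocol article*

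**What the plan says.** Three statements under Randomization in the protocol article matter here.

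- On entry: "Rolling recruitment will be implemented".
- On the scheme, a single block size is given: "block-randomized using an online randomization program into one of two wellness coaching conditions, in blocks of four, with a 1:1 allocation ratio".
- On control of the process: "The principal investigator will oversee the randomization process and will keep allocation concealed until baseline assessments have been completed".

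The same section says that the research assistants who collect assessment data are blinded throughout. Families cannot be, and they learn their condition after baseline. The principal investigator is not described as blinded.

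Under Recruitment, interested parents "will contact the principal investigator to obtain further information regarding the program and associated research study", and they also obtain "an anticipated timeline for when their assessments and home visits will begin". One role therefore oversees allocation and is the first point of contact for families.

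**The concern.** A small block of fixed, published size leaks information as it fills. Once one arm has used its two places, the remaining places in that block are settled. This matters when the person who can see earlier assignments also talks to families before they enter the trial, because a keen or hesitant family could be brought in sooner or later according to the arm expected next. Nobody need intend it.

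The measures exposed are those that depend on what kind of family lands in which arm: retention, session completion, satisfaction and change in health outcomes. The Background section hypothesises that both arms will succeed on retention, delivery and acceptance. The Discussion says each condition will be evaluated for its future potential. The Statistical analyses section derives effect sizes for later sample-size calculations. As an illustration of scale only: with 20 girls per arm, two families who would complete in place of two who would not move that arm's completion rate by 2/20 = 10 percentage points.

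**Working it through.** The article states no predictability figure, so there is none to reproduce. The check is an enumeration.

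**Inputs**
- Block size 4, ratio 1:1 (Randomization): two places per arm in each block.
- Sample size 40 (Study population): 40/4 = 10 complete blocks.
- Assumption, not stated in the article: the observer knows the block size and every earlier assignment in the current block.

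**Assignments known with certainty.** A block has C(4,2) = 6 equally likely orders. An assignment is certain when one arm already has both its places filled.

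| Place in block | Chance it is certain | Chance a best guess is right |
|---|---|---|
| 1 | 0 | 1/2 |
| 2 | 0 | 2/3 |
| 3 | 1/3 (first two match) | 1/3 + (2/3)(1/2) = 2/3 |
| 4 | 1 | 1 |

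- Expected certain per block: 0 + 0 + 1/3 + 1 = 4/3, and (4/3)/4 = 33.3%.
- Over 10 blocks: 10 × 4/3 = 13.3 of 40.
- Each block gives one certain assignment (probability 2/3) or two (probability 1/3), so the total runs from 10 (25%) to 20 (50%). The chance that it lies between 12 and 15 is 0.195 + 0.260 + 0.228 + 0.137 = 0.82.

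**Best-guess accuracy.** 1/2 + 2/3 + 2/3 + 1 = 17/6 correct per block, and (17/6)/4 = 17/24 = 70.8%. The general formula for block size 2m agrees: m + (2^(2m)/C(2m,m) − 1)/2 = 2 + (16/6 − 1)/2 = 2.833 of 4.

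**Alternatives, for an observer who still knows all earlier assignments.** For fixed blocks of size 2m the certain share is 1/(m+1). The varied-block rows come from a simulation (40 girls, 5,000 runs) in which the observer also knows the set of possible sizes.

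| Scheme | Certain | Best guess right |
|---|---|---|
| Fixed 4 (as stated) | 33.3% | 70.8% |
| Fixed 10 | 1/6 = 16.7% | 65.3% |
| One 20:20 list | 1/21 = 4.8% | 58.7% |
| Varied 4 or 6 | 5.6% | 68.9% |
| Varied 4, 6 or 8 | 2.3% | 67.7% |

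Varying the block size removes most of the certainty but little of the guessing advantage. Only keeping earlier assignments and the list from the person in contact with families addresses both.

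**The case against.** The strongest reply is that the article promises concealment, that an online program does the randomizing, and that a condensed article need not say who stores and releases the list. Several stronger readings do go beyond the text:

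- **That the principal investigator fixes start dates.** Recruitment says only that parents obtain an anticipated timeline from this role. Who sets the dates is not stated, and weekly visit times are agreed between coach and parent.
- **That the principal investigator enrols the girls or holds the list.** The text says this role oversees the process and keeps allocation concealed. That suggests access but does not state it.
- **That a third of assignments will be known outright.** The figure is an expectation for someone who knows all earlier assignments in the block. Baseline includes seven days of accelerometer wear according to the physical activity section, so families may overlap. A caller's place in the sequence may not be settled at the time of the call.
- **That the results are biased.** Nothing shows this. The calculation measures predictability and gives neither size nor direction of bias. Motive is weak, since both arms are expected to succeed. Age, BMI percentile and distance limits are objective, assessors are blinded, and the article admits that it lacks power to compare arms.

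These points limit the claim but do not remove it. The single block size and the overlap of roles are stated, not inferred from silence. The concealment promise covers a girl's own assignment until her baseline is done. It does not stop someone from working out the next place from completed places in a block of known size.

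**Conclusion.** The point holds as a weakness of the stated allocation procedure. With fixed blocks of four, an expected one third of assignments are deducible in advance and about seven guesses in ten are right, on condition that the person in contact with families knows the earlier assignments in the block. If that person never sees them, the figures do not apply. If that person could see the full list, more than a third could be known. The article settles neither case.

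The consequence is moderate. Selective order of entry could distort the arm-level feasibility measures and the preliminary effect sizes carried to the later trial. The number recruited and the time taken to recruit are unaffected. A reader might infer that allocation has been manipulated or that the arm comparisons are already biased; the document supports neither. The change is worth making because it is cheap.

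**What to change.** The Discussion indicates that some families have already completed the intervention, so this applies to assignments still to be made.

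1. Have an existing team member with no family contact set up and run the online program.
2. Release each assignment only after that girl's baseline is recorded as complete.
3. Keep the list from the principal investigator, who sees an assignment only once it is released.
4. Replace the fixed blocks of four with randomly varied, undisclosed sizes, for example 4, 6 and 8.

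Steps 1 to 3 do most of the work; step 4 mainly removes certainty. Where assignments have already been made, the report can state who could see the sequence and when.

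The cost is a change of program settings and one reassigned duty within the team. If recruitment stops partway through a block, the arms can differ by at most half the block: 8/2 = 4 girls with a largest size of 8, against 4/2 = 2 under the present scheme.

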### Wellness coaching interventions

For both the HEPA skills and HE coaching intervention conditions, college-aged female research assistants will undergo ethics training, plus three 1-h coach training sessions, to serve as wellness coaches and deliver 12 weekly one-on-one intervention sessions in the home of each participating child. Materials and lessons for the wellness coaching curriculum are adapted from “Health in the Classroom” [28] and other supporting educational materials as appropriate to the topic and age group of the client. The theoretical basis for the intervention development comes from social cognitive theory [29] and the self-determination theory [30]. Social cognitive theory posits that behavior, personal factors, and the environment have reciprocal effects on one another to determine human behavior. Within this intervention, personal factors targeted are self-efficacy, observational learning, and monitoring and regulation of behavior. Constructs from the self-determination theory include autonomy, relatedness, and competence, which are also targeted within both arms of the intervention. Training will take place before coaching sessions 1, 5, and 9. The wellness coach and parent will mutually agree upon meeting times, so that at least one parent is always present in the home during the session, although the parents will not be involved in the coaching sessions. There will be flexibility in scheduling, and parents will be given the option for these times to remain the same over the course of the 12 weeks or to change as schedules require.

For the HEPA skills coaching intervention, the coaches will use motivational interviewing techniques in applying the theoretical components of role modeling, outcome expectations, social support, autonomy support, relatedness, competence, and vicarious learning to build self-efficacy and motivation and enhance behavior change to promote health and wellness. The content and activities of the 12 visits are shown in the Additional file 1: Table S1. A main theme of the home visits will be physical activity promotion and fruit and vegetable snack consumption through skill-building activities in the home environment. The wellness coaches will help the girls to set wellness goals and to self-monitor their healthful eating and physical activity behavior. The girls will be taught kitchen skills for fruit and vegetable preparation, as well as enjoyable physical activities they can do at home. Finally, the wellness coach will complete the activities alongside the girls in order to provide a source of social support and role modeling for the promotion of physical activity and healthful eating.

The HE coaching intervention, the active comparison group, is designed to help girls set goals and self-monitor their behaviors with a more general focus on overall health promotion, not specifically on physical activity and dietary intake behaviors. Wellness coaches will work to educate girls on a range of relevant health promotion behaviors including tooth brushing, smoking prevention, and physical activity. Similar to the HEPA skills intervention, coaches are meant to provide social support and role modeling for practicing healthful behaviors but will not lead physical activities or snack preparations as they do in the HEPA skills condition. Over the 12 weeks of the intervention, the HE coaching sessions will focus on the discussion and understanding of a range of health topics and health behaviors, as well as their benefits, barriers, and change strategies.

In both arms of the intervention, the coaching visits will have specifically assigned primary activities and secondary activities, along with other supplemental activities that coaches may include during their time with the girls. In addition to the scheduled activities, coaches will also integrate discussion of school, well-being, emotions, and everyday difficulties of the girls within both arms of the intervention. In the HEPA skills intervention group, discretionary time that follows completion of the lesson for the day will be spent making choices for physical activity and fruit and vegetable snack for their next session or helping with homework, playing games, doing puzzles, or talking. In the HE group, wellness coaches will be able to spend any extra time helping with homework, playing games, doing puzzles, or talking.

